With the aim of coping with stressors or strains in the future, mental health literacy (MHL) is also an important concept. Adolescence is a period of significant risk for mental disorders [21]. However, if mentally ill, a large proportion of adolescents fail to obtain the needed mental health care. A recent review (based on 22 studies [22]) of perceived barriers and facilitators for mental health help-seeking in young people showed that perceived stigma and embarrassment, problems recognizing symptoms, and a preference for self-reliance were the most important barriers. However, perceived positive past experiences, social support, and encouragement from others were identified as facilitators of the help-seeking process. The review concluded that strategies for improving help-seeking in C&A should focus on improving MHL and reducing stigma. MHL has been defined as “knowledge and beliefs about mental disorders which aid their recognition, management or prevention” [23]. Following Jorm [23], MHL encompasses knowledge that is linked to the possibility of action to benefit one’s own mental health or that of others including knowledge of how to prevent mental disorders, recognition of when a disorder is developing, knowledge of help-seeking options and treatments available, knowledge of effective self-help strategies for milder problems, and first aid skills to support others who are developing a mental disorder or are in a mental health crisis. School-based MHL programs address basic concepts of mental health, provide strategies for help-seeking, or include activities for stigma reduction toward mental illness. However, programs are heterogeneous with regard to the focus of the interventions, duration, and dose (for a review, see [24]). For example, the HeadStrong intervention [25] is a universal, curriculum-based program on MHL, stigma, help-seeking, psychological distress, and suicidal ideation. Classroom activities are delivered by teachers over a period of 5–8 weeks in five modules (e.g., “Mood and mental wellbeing”, “Reaching out – helping others”). *The Guide* resource (teenmentalhealth.org) consists of six modules covering stigma and mental illness, understanding mental health and mental illness, information on specific mental illnesses, experiences of mental illness, help-seeking, and the importance of mental health [26]. Reviewing the effectiveness of school-based MHL programs (Cochrane criteria applied, 27 studies included), Wei and colleagues [24] state that even if most studies report improved knowledge (12 of 15 studies), changes in stigmatizing attitudes (14 of 21 studies), and/or enhanced help-seeking behavior (8 studies, of which 5 studies investigated attitudes toward help-seeking; results were mixed for different sources), the quality of the evidence is low. Methodological weaknesses include, but are not limited to, the lack of randomized controlled trials (RCTs), missing control for confounders (e.g., age, gender, mental health status), and the lack of validated measures. In addition, former reviews on school-based MHL interventions [27, 28] primarily criticize the quality of research designs (e.g., small sample sizes, lack of follow-ups). Regarding Internet resources, there are various websites to improve youth MHL skills (e.g., mindcheck.ca, foundrybc.ca; see [29]). Preliminary pilot data support the idea that brief Internet-based MHL interventions improve knowledge and help-seeking attitudes [30]. The topics covered were, for example, depression, anxiety, and suicide.

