### Enrollment and randomization

Permission to contact schools within the regional districts of all five recruiting study sites (Hamburg, Heidelberg, Leipzig, Marburg, Schwäbisch Gmünd) will be requested from federal authorities. A total list of schools in the regional districts will be acquired. Eligible schools will be contacted and informed, in random order, about the possibility to participate, until the prospected sample size is reached (in total *N* = 15,000 C&A). Following the baseline screening, healthy C&A (not fulfilling allocation criteria for any other ProHEAD program; see [31–34]) will be invited to participate in the *StresSOS* online program. C&A will receive an email including information about the trial and access details for the baseline assessment within the *StresSOS* trial. After completing this assessment, participants will be randomized with equal probability (in a 1:1 ratio) to the online *StresSOS* program and the online control group (online program on healthy nutrition). The allocation will be randomized, stratified for gender and school type. Randomization will be conducted externally and will follow a permutated block design with variable, randomly arranged block sizes. Following randomization, participants will be contacted informing them about their allocation to the respective intervention group and will receive access details for the specific online program.

In the face-to-face *StresSOS* program, the entire class will be invited to participate in the trial. Parallel to the online trial, eligible schools will be contacted and informed in random order about the possibility of participating in the program. Blinding is not possible. Participating C&A and experts are not unaware of the interventional procedure. However, assessments are based on self-report and take place within the school-based screening, which helps to avoid biased assessment of results.

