### Sample size calculation

In the control condition, 30% transitions from “healthy” to “at-risk” are expected. Further, it is anticipated that participation in *StresSOS* (online or face-to-face) will prevent 50% of these transitions, i.e., reduce the transitions to 15%. The sample size calculation is primarily based on the non-inferiority trial (Study B). Assuming equal efficacy for online and face-to-face delivery of *StresSOS* (i.e., 15% transition to “at-risk”), a non-inferiority margin δ = 5%, and an allocation ratio of 5:1, 2920 participants (2500 in the online and 420 in the face-to-face condition) need to be included in Study B to test non-inferiority with 80% power at α = 5% (Z-test). For Study A, the proposed sample size will allow one to assess the assumed group differences precisely (95% confidence interval (CI) +/− 2.3%); i.e., it allows one to test clinical significance of the efficacy of online *StresSOS* (between-group difference > 10%) with more than 95% power. The sample size may be larger, as all C&A who do not meet the inclusion criteria of the other four ProHEAD trials for C&A with (sub-threshold) mental health problems [31–34] are included. Even if the proposed sample size is reached, the program will still be offered to “healthy” C&A.

Based on previous experiences in school-based settings, there may be an expected loss to follow-up rate of 15% for the face-to-face sample [36] and 25% for the program-specific assessments of the online sample. Based on the literature [19] and the experiences within the consortium, the expectation is that about 33% of the participants in the online *StresSOS* condition will be compliant and work through the modules as expected, 33% will utilize about half of the modules, and 33% will log in only once.

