### Statistical analyses

#### Study A

Differences in the transition rate from the “healthy” group to the “high-risk” or the “mental health problems” group at 12 months follow-up will be tested with Fisher’s exact test (two- sided, α = 5%). The 95% CIs for the group difference will be calculated in order to test clinical significance (> 10% difference) of the online *StresSOS* efficacy. Analyses will be based on intention-to-treat (ITT) principles. Missing values will be imputed with the predictive mean matching method using the R package mice (Multivariate Imputation by Chained Equations [55]).

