#### Study B

Non-inferiority [56] of online delivery of *StresSOS* will be tested against the null hypothesis H0: Difference (% transitions face-to-face – % transitions online) < 5% (Z-test, α = 5%). Non-inferiority is assumed if the upper limit of the 95% CI of the empirical group difference is less than 5% (CI inclusion approach). Propensity score weighting methods will be applied to control for potential confounders between the online and the face-to-face condition [57]. The covariates taken into account for the propensity score procedure will be, for example, psychological strain, coping skills, age, gender, and type of school. Tests will be based on ITT principles; missing values will be imputed.

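### Study A's primary analysis is valid but leaves the baseline screening scores out of the comparison, which costs a little precision

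*Protocol article*

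**What the plan says.** The Study A paragraph under Statistical analyses says that the difference in transition rates "at 12 months follow-up will be tested with Fisher’s exact test (two- sided, α = 5" per cent. It then adds: "The 95% CIs for the group difference will be calculated in order to test clinical significance", with a difference above 10 points as the bar. Analysis is by intention to treat, and missing values are imputed by chained equations. No covariate is named for the test or the interval, and the predictors in the imputation are not listed.

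Enrollment and randomization states that, after a trial-specific baseline assessment, "participants will be randomized with equal probability (in a 1:1 ratio"), stratified by gender and school type. Inclusion and exclusion criteria makes entry depend on the baseline ProHEAD screening: only pupils who meet none of the criteria of the other four programmes are invited. Primary outcome measures defines the endpoint as meeting any of those programmes' criteria at 12 months and lists the SDQ, SEED, WCS, CRAFFT-d, AUDIT and PHQ-A.

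The planning values are in Sample size calculation: "In the control condition, 30% transitions from" healthy to at-risk among controls, and StresSOS expected to "reduce the transitions to 15" per cent. The arm sizes for Study B are "2500 in the online and 420 in the face-to-face condition". For Study A the section quotes a 95% CI of ±2.3 points and more than 95% power for a difference above 10 points.

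**The concern.** All pupils enter Study A below every cut-off, but some start close to one and others far from it. Starting level should help to predict who crosses a cut-off within a year, and it is measured at entry by the screening that later scores the endpoint. A comparison that ignores it leaves explainable variation in the standard error and lets chance imbalance in starting level pass into the estimate.

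The stake is the width of the interval that must clear 10 points. The plan assumes that StresSOS halves transitions, while the same section expects only about a third of online users to work through the modules as intended. A true difference smaller than 15 points is therefore a case worth planning for, and there the width of the interval matters.

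**Working it through.** **Inputs from the documents.** Control rate 0.30, StresSOS rate 0.15, 2500 pupils in the online arm and hence 2500 controls at 1:1, threshold 0.10, 95% CI.

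**Reproducing the plan's figures without covariates.**
- SE = √(0.30×0.70/2500 + 0.15×0.85/2500) = √(0.3375/2500) = 0.01162.
- Half-width = 1.96 × 0.01162 = 0.0228, or 2.28 points (stated: 2.3).
- Power for the 10-point criterion = Φ((0.15 − 0.10)/0.01162 − 1.96) = 99.0% (stated: more than 95%).

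The stated precision is therefore that of the unadjusted comparison.

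**How much could baseline scores explain?** The documents give no R², so this is an assumption shown as a range. I simulated a liability score at baseline and 12 months with correlation r and kept only pupils below a baseline cut-off (the healthy share). The top 30% or 15% at follow-up counted as transitions, and transition was regressed on the baseline score. The R² values for the two arms were pooled with weights 0.21 and 0.1275 (the outcome variances).

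| Healthy share | r = 0.4 | r = 0.7 |
|---|---|---|
| 35% | 0.022 | 0.084 |
| 50% | 0.027 | 0.105 |
| 65% | 0.035 | 0.130 |

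A second simulation (four domains, reliability 0.8, year-on-year stability 0.4–0.8, 26–28% transitions) gave R² of 0.029–0.107. A trial-level simulation (5000 pupils, 600 repeats) found the adjusted and unadjusted estimators unbiased for the same effect, with an SD ratio of 0.988. That is a 1.2% gain, near the bottom of the range. R² stays small partly because entry below every cut-off restricts the baseline range.

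**Effect on precision.** Adjusted SE = SE × √(1 − R²); equivalent unadjusted sample = 2500/(1 − R²).

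| R² | Half-width (points) | CI narrower by | Equivalent n per arm |
|---|---|---|---|
| 0 | 2.28 | – | 2500 |
| 0.02 | 2.25 | 1.0% | 2551 |
| 0.05 | 2.22 | 2.5% | 2632 |
| 0.10 | 2.16 | 5.1% | 2778 |
| 0.13 | 2.12 | 6.7% | 2874 |

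**Effect on power for the 10-point criterion.** Power = Φ((d − 0.10)/(SE_d × √(1 − R²)) − 1.96), where SE_d takes control rate 0.30 and StresSOS rate 0.30 − d. The values 12 and 13 points are illustrations and not planning assumptions. For d = 0.12, SE_d = √((0.21 + 0.18×0.82)/2500) = 0.01196; for d = 0.13, √((0.21 + 0.17×0.83)/2500) = 0.01185.

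| True difference | R² = 0 | 0.02 | 0.05 | 0.10 | 0.13 |
|---|---|---|---|---|---|
| 12 points | 38.7% | 39.3% | 40.3% | 42.2% | 43.4% |
| 13 points | 71.6% | 72.5% | 73.8% | 76.1% | 77.5% |
| 15 points (planned) | 99.0% | 99.2% | 99.3% | 99.5% | 99.6% |

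**Sensitivity to losses.** The 25% loss in the article refers to programme-specific assessments. If it applied to the primary endpoint (1875 per arm), the half-width would be 2.63 points, falling to 2.56–2.49 at R² 0.05–0.10. Power at 15 points would be 96.1%, rising to 96.9–97.6%.

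**The case against.** The strongest reply is that nothing here is wrong. Study A is individually randomised, the raw risk difference is unbiased for the intended marginal effect, and at the planning values power is 99.0% with or without covariates. All of that stands, so this can only be a point about efficiency. It does not dispose of the matter, because the article fixes the primary test and interval and the gain uses data already in hand.

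A reader might also infer that the plan contradicts itself, since Study B weights on "psychological strain, coping skills, age, gender, and type of school" and the Background reports earlier studies' "missing control for confounders (e.g., age, gender, mental health status"). The documents do not support that. Study B compares separately recruited samples, and both passages concern confounding, which randomisation handles in Study A. Neither implies that precision adjustment was thought necessary there.

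A reader might further infer that the ordinary test of difference would gain power from an adjusted interval alone. It would not: while Fisher's test is primary, its power is unchanged.

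Two further limits stand. Baseline scores may enter through the imputation model, whose predictor list is ordinary analysis-plan detail, although that would not adjust the comparison among observed pupils. The assessment schedule figure is not shown, so a baseline score on each instrument for each pupil is inferred from the eligibility and endpoint definitions.

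**Conclusion.** The point holds as a modest loss of efficiency in a valid analysis. Over an assumed R² of 0.02–0.13, the CI would be about 1–7% narrower, equivalent to about 2–15% more pupils, and the trial-level simulation supports the low end. No conclusion changes at the planned 15-point effect. If the true difference is 12–13 points, power for the 10-point criterion rises by roughly 1–5 percentage points for R² up to 0.10, and by just under 6 at the extreme (R² 0.13, 13 points). The size rests wholly on the assumed R². The direction rests on baseline scores having some predictive value and on their being available for nearly all randomised pupils.

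**What to change.** Before any outcome data are seen, pre-specify a standardised (g-computation) marginal risk difference for Study A. Take it from a logistic model with arm, the baseline screening scores (SDQ, PHQ-A, the eating-disorder measures including the SEED, and the alcohol measures) and age. Handle the WCS by gender, since Primary outcome measures describes it for women. Compute a robust or bootstrap SE in each imputed data set and pool over imputations.

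Use the resulting 95% CI for the 10-point criterion and its Wald test as the primary test of difference. Report the raw difference and Fisher's test as supportive. If Fisher's test stays primary, claim no power gain for the test of difference.

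The estimand and the 10-point criterion stay the same, and no new data are needed. The cost is small: the covariate model must be fixed in advance, and the analysis becomes slightly more complex.

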#### Study B

Non-inferiority [56] of online delivery of *StresSOS* will be tested against the null hypothesis H0: Difference (% transitions face-to-face – % transitions online) < 5% (Z-test, α = 5%). Non-inferiority is assumed if the upper limit of the 95% CI of the empirical group difference is less than 5% (CI inclusion approach). Propensity score weighting methods will be applied to control for potential confounders between the online and the face-to-face condition [57]. The covariates taken into account for the propensity score procedure will be, for example, psychological strain, coping skills, age, gender, and type of school. Tests will be based on ITT principles; missing values will be imputed.

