### Objectives

The aim of the study is the development, implementation, and evaluation of a health promotion program named *StresSOS* addressing stress management and MHL. It is planned to investigate the efficacy of Internet-delivered *StresSOS* compared to an active online control condition (Study A) and non-inferiority of *StresSOS* online delivery to *StresSOS* face-to-face delivery (Study B) with regard to a reduction of new incidence of mental health problems in C&A. The primary hypothesis is that significantly fewer C&A in the *StresSOS* group will transit from the “healthy” group to the “high-risk” or the “mental health problems” group at 12 months follow-up, when compared to a control group receiving an online program on healthy nutrition. Further, we will explore for whom the program is most effective (e.g., child demographics). The programs’ acceptability will be analyzed to identify factors supporting or hindering the implementation of the Internet-based or the face-to-face prevention program at schools. In addition, data will be collected on the cost of interventions and compared to the study outcomes to determine the cost-effectiveness ratio of interventions.

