### Measures

#### Primary outcome measures

The primary outcome is the number of C&A with transition from the “healthy” group to the “high-risk” or the “mental health problems” group at 12 months follow-up, i.e., the proportion of C&A fulfilling any of the criteria for at-risk C&A or for C&A with mental health problems outlined in the ProHEAD trials on general mental health problems, eating disorder symptoms, at-risk alcohol use, and depressive symptoms (see [31–34] in this issue). Data will be assessed in the school-based follow-ups at 1 and 2 years post-enrollment within the ProHEAD Consortium.

The measures include the following instruments. The *Strengths and Difficulties Questionnaire* (SDQ) [37] is a screening questionnaire for psychosocial problems in C&A. It comprises four sub-scales (emotional, conduct, hyperactivity, and peer problems), each scored on a scale from 0 to 10. Instruments specific for the assessment of eating disorder symptomatology include the *Short Evaluation of Eating Disorders* (SEED) [38] and the *Weight Concerns Scale* (WCS) [39]. The SEED assesses the three main symptoms for anorexia (degree of underweight, fear of weight gain, and distortion of body perception) and bulimia (amount of binge eating, amount of compensatory behavior, and over-concern with body shape and weight). The WCS uses five items to assess concerns with weight associated with body image in women. Instruments specific for the assessment of risky alcohol use and alcohol misuse include the *Car, Relax, Alone, Forget, Friends, Trouble* questionnaire (CRAFFT-d) [40] and the *Alcohol Use Disorders Identification Test* (AUDIT) [41]. The CRAFFT-d is a behavioral health screening tool for at-risk alcohol use. The AUDIT is a screening tool developed by the WHO to assess alcohol consumption, drinking behaviors, and alcohol-related problems. As the main instrument for the assessment of depressive symptoms, the *Patient Health Questionnaire-9 modified for Adolescents* (PHQ-A) [42] is used. The PHQ-A is a nine-item self-report instrument assessing the presence and severity of depressive symptoms based on the diagnostic criteria for depression according to the Diagnostic and Statistical Manual of Mental Disorders, fourth edition (DSM-IV) [43].

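### Study B's null hypothesis and confidence-interval rule are written in the wrong direction: with the printed contrast, an online program worse by the full margin would almost surely be declared non-inferior

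*Protocol article*

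**What the plan says.** The relevant statements are all in the Protocol article.

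- **Outcome** (Primary outcome measures): the "number of C&A with transition from the “healthy” group to the “high-risk” or the “mental health problems” group at 12 months follow-up". A higher percentage is worse.
- **Aim** (Objectives): online delivery is to be shown non-inferior to face-to-face delivery. Online is the new format and face-to-face the reference.
- **Margin** (Sample size calculation): "a non-inferiority margin δ = 5%, and an allocation ratio of 5:1", with 15% transitions assumed under both formats.
- **Hypothesis** (Statistical analyses, Study B): the "null hypothesis H0: Difference (% transitions face-to-face – % transitions online) < 5" per cent, by Z-test at α = 5%.
- **Decision rule** (same paragraph): "Non-inferiority is assumed if the upper limit of the 95% CI of the empirical group difference is less than 5" per cent.

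The hypothesis sentence gives the only definition of the group difference, face-to-face minus online. No other section reverses it.

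**The concern.** Write D for face-to-face minus online. Three things are wrong.

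1. **The interval rule tests the wrong format.** When online is worse, D is negative, and the worse online is, the more easily the upper limit of D stays below +5 points. Meeting the rule rules out face-to-face being 5 or more points worse than online. It says nothing about how much worse online may be.
2. **The null is not a non-inferiority null.** D < 5% contains equality of the two formats and every case in which online is worse. Rejecting it would require showing that online is better by at least 5 points.
3. **The two sentences contradict each other.** The interval rule declares success when the whole confidence interval lies inside the region called H0, that is, when the data support the null.

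Non-inferiority is one of the two main objectives, and the sample size calculation is based primarily on it. If the printed rule were applied, an inferior online program would pass and a better one would usually fail. If it were not applied, the direction of the test could be settled after the data are seen.

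**Working it through.** **Inputs.** From Sample size calculation: 2500 online and 420 face-to-face participants, margin 5 points, 15% transitions in both formats, 80% power, α = 5%, and expected losses of 15% (face-to-face) and 25% (program-specific assessments online). From Study B: D = face-to-face minus online, 95% confidence interval, limit +5 points. Online rates of 10%, 20%, 25% and 30% are illustrative; 20% is exactly the margin above 15%.

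**The plan's own figure.** At 15% in both arms,

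SE = √[0.15 × 0.85 × (1/420 + 1/2500)] = 0.01883.

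Power = Φ(0.05/0.01883 − z):

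- one-sided 5%: Φ(2.655 − 1.645) = 84.4%
- 95% interval (one-sided 2.5%): Φ(2.655 − 1.96) = 75.7%

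Taking the losses off (420 × 0.85 = 357; 2500 × 0.75 = 1875), one-sided 5% gives 79.7% with 357/2500 and 78.2% with 357/1875. The stated 80% is therefore reproduced with one-sided 5% after loss. At a true difference of zero, power is the same whichever way the difference is taken, so the direction error does not affect the sample size.

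**The decision rules.** With SE = √[p_f(1 − p_f)/420 + p_o(1 − p_o)/2500], where p_f and p_o are the face-to-face and online rates:

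- rule as printed, upper limit of D below +5 points: Φ((0.05 − D)/SE − 1.96)
- correctly directed rule, upper limit of −D below +5 points: Φ((0.05 + D)/SE − 1.96)
- printed H0 rejected, lower limit of D above +5 points: Φ((D − 0.05)/SE − 1.96)

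For online 20% and face-to-face 15%, D = −0.05 and

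SE = √(0.1275/420 + 0.16/2500) = 0.01917.

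- Printed rule: Φ(0.10/0.01917 − 1.96) = Φ(3.26) = 99.9%.
- Correct rule: Φ(0 − 1.96) = 2.5%.

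Results with face-to-face fixed at 15%:

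| Online | D (points) | SE | Printed rule declares | Correct rule declares | Printed H0 rejected |
|---|---|---|---|---|---|
| 10% | +5 | 0.01843 | 2.5% | 99.97% | 2.5% |
| 15% | 0 | 0.01883 | 75.7% | 75.7% | about 0 |
| 20% | −5 | 0.01917 | 99.9% | 2.5% | about 0 |
| 25% | −10 | 0.01946 | about 100% | about 0 | about 0 |
| 30% | −15 | 0.01969 | about 100% | about 0 | about 0 |

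A simulation of 400,000 trials at 20% against 15% gave 99.9% for the printed rule and 2.0% for the correct one.

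**Sensitivity at 20% against 15%, printed rule.** With the stated losses (357/1875): 99.7%. With an assumed design effect of 2 in the face-to-face arm, because whole classes are invited: 97.1% at 420/2500 and 94.3% at 357/1875.

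**The case against.** The strongest defence is that these are slips of notation and the intent is clear. Three arguments support it.

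- **A missing minus sign.** With face-to-face minus online, a proper null is D ≤ −5%. The printed null has that contrast and that direction of inequality; apart from the boundary, only a minus sign before the 5 is absent.
- **An unstated order of subtraction.** The interval sentence does not repeat which arm is subtracted from which. Read as online minus face-to-face, it is exactly the right rule. The 99.9% therefore depends on carrying the printed contrast into that sentence. The literal null fails the other way, being almost never rejected when online is worse.
- **Idealised figures.** The calculation ignores propensity weighting, clustering in classes and loss.

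Most of this is fair as an account of how the error arose, and the intended direction is not in doubt. It does not clear the text. Adding the minus sign to the null leaves the interval rule wrong for the only difference defined. Reversing the interval contrast leaves the null wrong and opposed to the rule. Both sentences come right only if the null is edited and the order of subtraction is also changed between two adjacent sentences. The loss and clustering checks lower 99.9% to between 94.3% and 99.7%, which leaves the conclusion unchanged.

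**Conclusion.** The concern holds. As printed, the Study B null is not a non-inferiority null, the interval rule applied to the defined difference tests the wrong format, and the two sentences conflict. Using that rule with the printed contrast, a online program worse by exactly the margin is declared non-inferior with probability 99.9% instead of 2.5%, and one that is 5 points better with probability 2.5% instead of 99.97%.

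These figures assume 420 and 2500 independent, unweighted observations and a 15% face-to-face rate. They describe the interval rule only; the literal null errs in the opposite direction. The direction of the error does not depend on these assumptions. It must be corrected before the Study B analysis.

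**What to change.** Replace the hypothesis and decision sentences in Statistical analyses, Study B, with:

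- H0: (% transitions online − % transitions face-to-face) ≥ 5 percentage points.
- H1: (% transitions online − % transitions face-to-face) < 5 percentage points.
- Non-inferiority of online delivery is concluded if the upper confidence limit of online minus face-to-face is below +5 percentage points.

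If the face-to-face minus online order is kept, the equivalent is H0: difference ≤ −5 points, with non-inferiority concluded if the lower limit is above −5 points. Reversing the contrast while leaving H0 as < 5% is not enough, because that statement is the non-inferiority claim itself and belongs in H1.

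The cost is two rewritten sentences, carried into the SAP, with no change to sample size, data collection or conduct. The Trial status section reports that recruitment had not begun, so the correction could be made before any outcome data existed; if data have since accrued, date and record it before outcomes are compared by format.
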